#### Modifications

If they wish to do so, subjects can leave the study at any time for any reason without any consequences. Additionally, the investigator can decide to withdraw a subject from the study for urgent medical reasons. Subjects in the watchful waiting group may need to undergo surgery because of persisting complaints. As in all surgical trials, we expect about 30 % of patients to switch from watchful waiting to surgery. Patients wishing to cross-over from watchful waiting to surgery will be monitored for the complete follow-up period.

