#### Secondary outcome measures

Secondary outcome measures comprise:Other health-related quality of life measures, i.e., the EuroQol-5 Dimensions-3 Levels (EQ-5D-3 L), the Sino-Nasal Outcome Test-22 (SNOT-22), and the Nasal Obstruction Symptom Evaluation scale (NOSE);Nasal patency as measured with four-phase rhinomanometry and peak nasal inspiratory flow;Complications and potential side effects;Cost-effectiveness.

The EQ-5D-3 L consists of a descriptive part and a visual analogue scale (VAS). The descriptive part comprises the following five dimensions: mobility, self-care, usual activities, pain/discomfort, and anxiety/depression. The VAS records the respondent’s self-rated health on a vertical scale ranging from 0 (worst imaginable health state) to 100 (best imaginable health state) [24]. The SNOT-22 is developed as a patient-reported outcome measure to use in chronic rhinosinusitis with or without nasal polyposis and covers a broad range of health and health-related quality of life problems, including physical problems, functional limitations, and emotional consequences [25, 26]. The NOSE is developed to assess nasal obstruction and is validated in adults undergoing septoplasty [16, 27].

The physician researcher, who performs four-phase rhinomanometry and peak nasal inspiratory flow measurements, has been trained in the use of both devices. The rhinomanometer was produced by the RhinoLab GmbH, Freiburg im Breisgau, Germany, and supplied by Dos Medical BV, ‘s-Hertogenbosch, the Netherlands. The inspiratory flow meter was produced by Clement Clarke International, Essex, United Kingdom, and supplied by PitMedical BV, Enschede, the Netherlands.

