### Statistical methods

#### Outcomes

Effects of surgery on health-related quality of life and nasal passage (rhinomanometry and peak nasal inspiratory flow) will be calculated as mean differences with 95 % confidence intervals. For health-related quality of life, short-term and long-term effects will be evaluated at 3, 6, 12, and 24 months follow-up, respectively. All analyses will be performed on an intention-to-treat basis. In addition to the intention-to-treat analysis, we will perform two sensitivity analyses: 1) a per-protocol analysis in which we will exclude adults in the watchful waiting group, who crossed-over to surgery, and 2) an “as treated” analysis in which we will add adults in the watchful waiting group, who crossed-over to surgery, to the septoplasty group. Potential modification of the effect of septoplasty will be evaluated using Poisson regression including interaction terms for gender, age, and severity of the septal deviation.

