### Harms

Septoplasty may lead to the following complications: nasal obstruction, nasal septal hematoma, nasal septal abscess, saddle nose or other nasal deformity, nasal septal perforation, epistaxis, acute or chronic rhinitis. All these complications are rare (occurring in less than 1 % of all cases) and most of them resolve without additional treatment. In selected cases, an additional intervention (drainage of hematoma or abscess, antibiotics, additional nasal packing, surgical correction of saddle nose or other nasal deformities) may be needed to resolve the complication. All adverse events (AEs) will be followed until they have abated, or until a stable situation has been reached. Depending on the event, follow-up may require additional tests or medical procedures as indicated, and/or referral to the general physician or a medical specialist. SAEs will be reported until the end of the study.

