## Discussion

This ongoing pragmatic randomized controlled trial is the first study to assess the effectiveness of septoplasty compared to non-surgical management for nasal obstruction due to a deviated nasal septum in adults. So far, all available evidence for the effectiveness of septoplasty is based on observational studies. Observational studies, however, are known to have a high risk of bias. As a result, the beneficial effects of septoplasty that were reported in previous studies are possibly overestimated, since the improvement after surgery could also be explained by other factors, such as natural history or extraneous effects. To assess the effectiveness of interventions and to inform decisions about treatment options in clinical practice, a pragmatic randomized controlled trial remains the design of choice [31].

A major strength of our study is that the effectiveness of septoplasty is evaluated both in terms of subjective (health-related quality of life) as well as objective (nasal patency) outcome measures. Health-related quality of life is measured with four widely used questionnaires and nasal patency is assessed by two different methods (four-phase rhinomanometry and peak nasal inspiratory flow). Although subjective and objective outcome measures both provide valuable information about the effects of septoplasty on nasal obstruction, it is known that subjective and objective outcomes do not necessarily correlate [11]. We chose health-related quality of life as primary outcome measure to focus on the patient rather than the disease, as septoplasty aims at improving nasal symptoms and not merely straightening the nasal septum.

Another strength of our study is the relatively long duration of follow-up, i.e., 2 years for each participant. Follow-up visits will be scheduled at baseline and after 3, 6, 12, and 24 months. Most studies performed so far have a follow-up varying between 3 months and 1 year. This provides a distorted view of the effectiveness of surgery, as long-term results tend to differ from short-term outcomes, especially for turbinate surgery [32]. A follow-up of 2 years was chosen for this trial in order to evaluate whether short-term effects of surgery remain present after a longer period of time. Moreover, it provides insight in the number of patients wishing to cross-over from watchful waiting to surgery after the first year of follow-up.

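### Analysing complications by randomised arm, with about 30% of controls expected to be operated on, dilutes the between-arm excess risk to about 0.7 of its size

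*Protocol article*

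**What the plan says.** Under Secondary outcome measures, the protocol article lists "Complications and potential side effects". Under Statistical methods, Outcomes, it fixes the analysis population in one sentence: "All analyses will be performed on an intention-to-treat basis". The Methods/Design part of the abstract repeats the rule. Neither place makes an exception for safety.

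The same Outcomes paragraph adds two sensitivity analyses. One is per-protocol and drops controls who crossed over. The other is an as-treated "analysis in which we will add adults in the watchful waiting group, who crossed-over to surgery, to the septoplasty group". The paragraph opens with quality of life and nasal passage. It does not mention complications, and it does not say whether the sensitivity analyses extend to them.

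Under Modifications, the protocol says "we expect about 30 % of patients to switch from watchful waiting to surgery", without a time horizon, and then: "Patients wishing to cross-over from watchful waiting to surgery will be monitored for the complete follow-up period". Complications of cross-over operations will therefore be observed.

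The Harms section lists seven complications of septoplasty: obstruction, haematoma, abscess, saddle nose or another deformity, perforation, nosebleed and rhinitis. It puts their frequency below 1%.

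**The concern.** The complications in the Harms section are presented as consequences of the operation. When roughly three in ten controls have that operation, a by-arm table credits some surgical harm to the policy of not operating, and the contrast between the arms shrinks. The table also splits the operated patients across two columns, so neither column gives the complication rate of all operations in the trial.

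This matters because the trial is meant to feed guidelines on when septoplasty is indicated. A guideline reader needs two things: what follows from a policy of operating now rather than waiting, and how often an operation causes harm. The intention-to-treat table answers the first. Nothing in the stated rule makes the second a main analysis.

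**Working it through.** The protocol gives no by-arm figure for complications, so there is no stated result to reproduce. The calculation uses its own inputs.

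**Inputs from the protocol article**
- At least 100 patients per arm (Sample size).
- Cross-over share c = 0.30 (Modifications).
- Complication frequency below 1% (Harms). This can be read as the combined rate or as the rate of each of the seven items. The upper bounds are then p = 1% combined, or 7 × 1% = 7% if the items never coincide.

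**Assumptions of this check**
- Everyone in the septoplasty arm is operated on.
- The risk p is the same in cross-overs as in the septoplasty arm.
- These complications do not occur without surgery.

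**By randomised arm**
- Septoplasty arm: rate p.
- Watchful-waiting arm: rate c × p = 0.3p.
- Difference: p − 0.3p = 0.7p.

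**By surgery received**
- Operated: 100 + 0.30 × 100 = 130 patients, rate p.
- Not operated: 70 patients, rate 0.
- Difference: p.

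| p | Expected events, septoplasty arm (of 100) | Expected events, watchful waiting (of 100) | Difference by arm (points) | Difference by surgery received (points) |
|---|---|---|---|---|
| 0.5% | 0.5 | 0.15 | 0.35 | 0.5 |
| 1% | 1.0 | 0.3 | 0.7 | 1.0 |
| 5% (illustration) | 5.0 | 1.5 | 3.5 | 5.0 |
| 7% | 7.0 | 2.1 | 4.9 | 7.0 |

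The proportional shrinkage equals c whatever the value of p: 20% if c = 0.20, 30% if c = 0.30 and 40% if c = 0.40.

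**Operations left out of the septoplasty-arm rate:** 30/130 = 23%.

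**Chance that at least one surgical complication appears under watchful waiting:** 1 − (1 − p)^30. This is 26% at p = 1% and 89% at p = 7%.

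**Precision of the rate per operation.** With zero events, the exact upper two-sided 95% limit is 1 − 0.025^(1/n). For n = 100 it is 3.6%, and for n = 130 it is 2.8%.

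**Time origin.** The as-treated analysis, as described, moves a cross-over patient into the septoplasty group as a whole. Two of the seven listed complications, obstruction and rhinitis, can also be present before surgery, and obstruction is the condition for entering the trial. Without a count that starts at the operation, pre-operative complaints of a cross-over patient can be recorded as surgical complications.

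**The case against.** The strongest reply has four parts.

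First, the Outcomes paragraph never names complications, and a journal article commonly leaves the safety population to the analysis plan, which is not shown. This stands in part. How complications are tabulated is indeed left open, but the rule on the population is not: it says all analyses, and the abstract repeats it. A later plan analysing complications by surgery received would depart from that published rule.

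Second, if the rule reaches complications, so does the as-treated analysis in the next sentence. Under the assumptions above it gives 1.3 expected events in 130 operated patients against none in 70 at p = 1%, which recovers the full difference. This largely stands. What remains is its rank as a sensitivity analysis, the missing link to complications and the missing time origin.

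Third, intention-to-treat is a valid answer to the pragmatic question of surgery against non-surgical management as the initial policy, with later surgery part of that policy. This stands, and it is why the by-arm table should be kept.

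Fourth, if the 1% limit is the combined rate, only about 0.3 events are expected in the wrong column. This also stands, and it limits the weight of the point.

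A reader might go further and infer that the trial would understate the risk of surgery itself. The documents do not support that. Control cross-over leaves the rate in the randomised septoplasty arm at p; that rate merely rests on fewer operations. A reader might also infer that late cross-overs would have almost no post-operative observation, because "SAEs will be reported until the end of the study". The Discussion only says that follow-up will show "the number of patients wishing to cross-over from watchful waiting to surgery after the first year of follow-up" and gives no expected number. The Harms section also has adverse events followed until they have settled or stabilised. Nor does the protocol say how many septoplasty-arm patients might never be operated on, so no case can be built on them.

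**Conclusion.** The concern holds as a point about the between-arm comparison and about completeness. Under the stated rule, and with the expected 30% cross-over, the excess complication risk is diluted to about 0.7p, and 23% of operated patients fall outside the septoplasty-arm rate. In absolute terms, the loss is 0.3 points at p = 1% and at most 2.1 points if the limit of 1% applies to each of the seven complications. These figures rest on equal risk in cross-overs, no such complications without surgery, and full uptake of surgery in the septoplasty arm.

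The existing as-treated analysis would recover most of the loss if it were applied to complications, but the protocol does not say that it will be. The point is minor to moderate and does not threaten the primary outcome.

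**What to change.** Add a sentence to the Outcomes part of Statistical methods that exempts complications from the intention-to-treat rule. For example: the main analysis of complications is by surgery received and includes every patient operated on, in either arm, with events counted from the date of operation; a table by randomised arm is given as a supplementary comparison of the two strategies.

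The cost is one extra table and the date of operation for every operated patient. Participant timeline provides for a standardised operation report, but mentions it directly after the scheduling of the surgical group, so it should be confirmed that the report also covers cross-over operations. No extra patients or visits are needed.

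The drawback is that any contrast between operated and unoperated patients is not randomised, because controls who cross over do so for persisting complaints. The result should therefore be presented mainly as a rate per operation with its confidence interval.

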### Participant timeline

With their informed consent, contact details of potential candidates will be communicated to the trial center by otorhinolaryngologists in the participating hospitals. Subsequently, patients will be contacted by phone by one of the researchers. The researcher will provide detailed information concerning the trial, answer questions, and check inclusion and exclusion criteria. When the patient agrees to participate, a baseline visit will be scheduled. At this visit, informed consent documents will be signed and baseline measurements will be performed, consisting of generic and disease-specific health-related quality of life questionnaires, disease-specific symptom scores, an ENT examination including anterior rhinoscopy and nasal endoscopy, four-phase rhinomanometry, and peak nasal inspiratory flow measurements^1^. Subsequently, the patient will be randomized to either septoplasty, with or without concurrent turbinate surgery as originally indicated by the otorhinolaryngologist, or a non-surgical watchful waiting strategy. The patient’s otorhinolaryngologist will be notified of the result of randomization. If the patient is assigned to the surgical group, septoplasty is scheduled by the otorhinolaryngologist within 6 to 8 weeks. A detailed and standardized operation report will be kept. During the study, patients and otorhinolaryngologists will be encouraged to manage nasal obstruction according to their regular practice. If the medical condition of a patient warrants attention during follow-up, the study physician will refer the patient to his or her local otorhinolaryngologist for further management. If the otorhinolaryngologist decides to perform septoplasty on a patient in the watchful waiting group (because of severe complaints persisting under non-surgical management), this patient will be classified as cross-over and monitored as planned. All included patients will be invited for follow-up visits at 3 months, 6 months, 12 months, and 24 months. During these four follow-up visits, the same questionnaires and measurements of the baseline visit are scheduled. Patients will be instructed to record health-related costs in a patient-based diary, which will be handed in and checked during each follow-up visit. Figure 1 shows a flowchart of our trial.

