### Sample size

Calculations of group size are based on a clinically relevant improvement on the Glasgow scale of 10 (standard deviation 15). Assuming a quality of life of 70 in the non-surgical group, and taking an alpha of 0.05 and a power of 0.90, each treatment arm should include at least 48 patients. We also performed a power calculation for the objective rhinomanometry measurements. The mean value of four-phase rhinomanometry in patients is about 2.6 Pa/cm^3^.s^-1^ (standard deviation 2). Since the mean value in asymptomatic patients is considered to be about 1.5 Pa/cm^3^.s^-1^, we assume an improvement of 1 Pa/cm^3^.s^-1^ to be clinically relevant. Taking an alpha of 0.05 and a power of 0.90, each treatment arm should include at least 70 patients. To allow for subgroup analyses according to gender, age, and severity of the septal deviation, we will include at least 100 adults in each treatment arm.

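### The per-protocol and as-treated analyses select on a poor course after randomisation, so both are expected to be biased against septoplasty and do not test the robustness of the intention-to-treat result

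*Protocol article*

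**What the plan says.** The protocol article, under Statistical methods, Outcomes, puts all analyses on an intention-to-treat basis and adds two sensitivity analyses. The first is "a per-protocol analysis in which we will exclude adults in the watchful waiting group, who crossed-over to surgery". In the second, the as-treated analysis, "we will add adults in the watchful waiting group, who crossed-over to surgery, to the septoplasty group". Both rules act on watchful-waiting patients only, and as printed neither gives a date by which surgery counts as cross-over.

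On how many will cross over, the Modifications section states that "we expect about 30 % of patients to switch from watchful waiting to surgery" and gives persisting complaints as the reason. The Participant timeline section describes the decision to operate on a watchful-waiting patient as taken "because of severe complaints persisting under non-surgical management". The primary time point is one year after inclusion and follow-up runs to 24 months. The Discussion foresees that some patients will want to switch after the first year.

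**The concern.** A patient who crosses over for persisting severe complaints is, on average, one who was doing badly without surgery. Dropping such patients from the control arm leaves the better-faring controls to be compared with an unselected surgical arm. Moving them into the septoplasty group does the same to the controls and may also add patients with a poorer prognosis to the surgical side. Either way the randomised comparison is lost, and the expected error runs against surgery.

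These are the only analyses that the article names for dealing with cross-over. ITT is itself diluted by cross-over, so readers will look to these two for the effect without dilution. If all three estimates come out modest, the agreement could be mistaken for robustness, although two of the three share a predictable bias and answer a different question from ITT.

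**Working it through.** **Inputs from the protocol.** Sample size section: difference 10, SD 15, control mean 70, alpha 0.05, power 0.90, at least 100 per arm. Modifications section: about 30% cross-over.

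**The plan's own figure.** n per arm = 2 x (1.960 + 1.282)^2 x 15^2 / 10^2 = 47.3, rounded up to 48 (two-sided). This reproduces "taking an alpha of 0.05 and a power of 0.90, each treatment arm should include at least 48 patients".

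**Assumptions not in the documents.**
- All 30% have crossed over by 12 months.
- They are the lowest 30% on an index that correlates rho with the outcome without surgery.
- Outcomes are normally distributed.
- Cross-overs have the full effect of surgery by the time of measurement.
- In the base case, surgery adds 10 points for everyone.

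**Shift in the control arm.** The normal density at the 30th percentile is 0.3477. Controls who do not cross over lie above the control mean by rho x 15 x 0.3477 / 0.70 = 7.45 x rho points. Those who cross over lie below it by rho x 15 x 0.3477 / 0.30 = 17.38 x rho points.

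**Expected estimates, constant effect.**
- ITT: 80 - (70 + 0.30 x 10) = 7.0, whatever rho is.
- Per-protocol: 80 - (70 + 7.45 x rho) = 10 - 7.45 x rho.
- As-treated: the surgical group falls by 0.30 x 17.38 x rho / 1.30 = 4.01 x rho, so the estimate is 10 - (7.45 + 4.01) x rho = 10 - 11.46 x rho.

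| rho | ITT | Per-protocol | As-treated |
|---|---|---|---|
| 0 | 7.0 | 10.0 | 10.0 |
| 0.2 | 7.0 | 8.5 | 7.7 |
| 0.4 | 7.0 | 7.0 | 5.4 |
| 0.6 | 7.0 | 5.5 | 3.1 |

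**Where each falls below ITT.** Per-protocol: 3 / 7.45 = 0.40. As-treated: 3 / 11.46 = 0.26.

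**If the effect varies.** Simulation with a correlation of 0.7 between the outcomes with and without surgery, at rho 0.2 / 0.4 / 0.6, gives:
- ITT 6.7 / 6.4 / 6.1
- per-protocol 8.5 / 7.0 / 5.5
- as-treated 7.9 / 5.9 / 3.9
- ITT / 0.70 (the complier estimate) 9.5 / 9.1 / 8.7

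The complier values match the simulated true effect in patients who would not cross over (9.5 / 9.1 / 8.7). That is below the all-patient effect of 10.

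**If fewer cross over by 12 months.** With 15%, an assumed figure, the density is 0.233 and the control shift is at most 15 x 0.233 / 0.85 = 4.1 points instead of 7.45.

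**Precision at 100 per arm.** The SE for ITT is 15 x sqrt(2/100) = 2.12. The SE for the complier estimate is about 2.12 / 0.70 = 3.03. The test statistic is unchanged: 7 / 2.12 = 10 / 3.03 = 3.30. Power for ITT at a difference of 7 is 91.0%.

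**The case against.** The strongest reply is that the primary analysis is sound. ITT is primary, it keeps about 91% power even when 30% cross over, and nothing in the article lets a sensitivity analysis override it. That stands.

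The second reply is that the size of the bias is unknown. Rho is not in the protocol. The text also speaks of patients wishing to cross over, and the Discussion notes that non-surgical care may be seen as the less desirable option. Switching driven by preference would make rho smaller, and at rho 0 both analyses are unbiased. The 30% is tied to no visit. All this stands as a limit on size. It does not remove the direction, because the stated reason for cross-over is a poor course.

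Three stronger readings are tempting, and the document does not support them:
- A reader might infer that both analyses must come out below ITT, or can say nothing about the undiluted effect. With weak selection both are biased yet lie nearer to 10 than ITT does.
- A reader might infer that septoplasty-arm patients who are never operated on will be counted as treated. The article is silent on them, and an article may leave this to the full protocol or analysis plan.
- A reader might infer that a complier estimate recovers the hypothesised 10 points. It does so only if the effect is the same for everyone.

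Finally, the instrument requires allocation to act on the outcome only through surgery. Patients are unblinded, the outcome is self-reported and concomitant medication is free, so this is uncertain. It is a good reason not to let the complier estimate displace everything else.

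**Conclusion.** The point holds for direction and only conditionally for size. By the protocol's own account of why patients cross over, the per-protocol and as-treated analyses select on a poor course after randomisation in one arm, and both are expected to understate the benefit of septoplasty. As-treated is the more affected of the two when prognosis carries over to the outcome after surgery. Neither tests the robustness of ITT.

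Under a benefit of 10, SD 15, a constant effect and 30% crossing over by 12 months, the bias is 7.45 x rho points for per-protocol and 11.46 x rho for as-treated. ITT averages 7.0. The two analyses fall below it only above rho of about 0.40 and 0.26 respectively. These thresholds and sizes rest on the assumptions listed. The bias is smaller if fewer patients have crossed over by the visit analysed. The primary ITT comparison is not affected.

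**What to change.** 1. Keep ITT as the primary analysis.
2. Add a complier-average estimate with randomisation as instrument: two-stage least squares on surgery received by the visit analysed (12 months for the primary outcome), adjusted for baseline.
3. Define cross-over by that visit, so that later surgery does not reclassify a patient in an earlier comparison.
4. Keep per-protocol and as-treated as descriptive analyses only, with a sentence stating that selection on poor course is expected to bias both against septoplasty.

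The cost is wording and one standard regression. Operation reports, diaries and medical records are already planned as sources on surgery. The drawbacks should be written into the plan. The interval is wider (SE about 3.0 against 2.1 points). If the effect varies, the estimate applies only to patients who would not cross over. The assumption that allocation acts only through surgery should be stated as uncertain in this unblinded trial with self-reported outcomes.

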### Outcomes

#### Primary outcome measure

Primary outcome measure will be the difference between both treatment arms in health-related quality of life, measured using the Glasgow Benefit Inventory (GBI) and Glasgow Health Status Inventory (GHSI) questionnaires, at the primary time point of 1 year after inclusion. While the GHSI gives a general measure of health status of a person at any specific time, the GBI is maximally sensitive to a change in health status caused by a specific event (e.g., surgical intervention) and can be administered postoperatively to measure the effect of the intervention on a patient’s quality of life [23]. Health-related quality of life was chosen as primary outcome measure, since septoplasty aims at improving nasal symptoms rather than merely straightening the nasal septum. Due to the dual chamber design of the nose, clinical practice shows no clear correlation between objective (e.g., nasal patency) and subjective results of septoplasty (e.g., patient sensation of airflow through the nose) [11]. Moreover, nasal septal deviation with concurrent reduction of nasal passage can be observed in asymptomatic subjects, while other subjects with comparable deviations may suffer from severe complaints. Apparently, what matters is not the nasal passage itself, but the effect the nasal passage has on someone’s well-being and daily life. Using quality of life measures in clinical practice ensures that treatment and evaluation focus on the patient rather than the disease. In addition, by using quality of life as primary outcome measure, we facilitate the comparison of treatment effects resulting from septoplasty with treatment effects of other procedures.

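### Effect modification of continuous outcomes is assigned to Poisson regression, which does not match the trial's mean-difference effect and, with model-based standard errors, inflates false-positive interactions

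*Protocol article*

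**What the plan says.** In the protocol article, Statistical methods, Outcomes, the quality-of-life instruments and the airflow measurements share one effect measure: "nasal passage (rhinomanometry and peak nasal inspiratory flow) will be calculated as mean differences". Confidence intervals are at the 95% level. The same paragraph closes with: "Potential modification of the effect of septoplasty will be evaluated using Poisson regression including interaction terms for gender, age". Deviation severity is the third modifier listed. That sentence gives no outcome, no link function and no variance estimator.

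Under Primary outcome measure, the primary comparison between the arms is on a quality-of-life outcome that is "measured using the Glasgow Benefit Inventory (GBI) and Glasgow Health Status Inventory (GHSI) questionnaires, at the primary time point of 1 year after inclusion". On the first instrument the section says that "the GBI is maximally sensitive to a change in health status caused by a specific event", and that it can be given after the operation. The article states no score range for it.

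Under Sample size, group size rests on a "clinically relevant improvement on the Glasgow scale of 10 (standard deviation 15"), with a mean of 70 in the non-surgical group. A second calculation uses a rhinomanometry mean of about 2.6 and SD 2. The two calculations give 48 and 70 per arm. The number is then raised to at least 100 per arm to allow subgroup analyses by gender, age and deviation severity, the three modifiers named in the Poisson sentence.

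**The concern.** The outcomes that the paragraph names are scores or physical measurements, and their effect is a difference in means. Poisson regression is a model for counts, and it departs from that setting in two ways.

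- **Variance.** It takes the variance to equal the mean. Where the true variance is larger, model-based standard errors are too small and interactions look more certain than they are. The ratio of variance to mean also depends on the unit of measurement, so the p-value for the same airflow data would change with the unit.
- **Scale.** With its usual log link, an interaction is a ratio of ratios of means. A benefit that is constant in points then appears as effect modification whenever the subgroups differ in level.

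The trial aims to inform guidelines on indications for septoplasty. A false modifier could influence who is thought to benefit from surgery, and the final sample size was justified by exactly these analyses.

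**Working it through.** **Inputs.** From Sample size: Glasgow difference 10, SD 15, control mean 70 (so 80 with surgery, midpoint 75); alpha 0.05; power 0.90; rhinomanometry mean 2.6, SD 2, relevant improvement 1; 100 per arm. Sample size speaks only of the Glasgow scale and does not say which of the two instruments the figures describe.

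**1. The protocol's own figure.** Two-sided comparison of two means: n = 2 × (1.960 + 1.282)² × 15² / 10² = 47.3, rounded up to 48 per arm, as stated. The protocol therefore itself treats the Glasgow score as continuous with a difference in means.

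**2. Size of a nominal 5% interaction test with model-based Poisson errors.** The standard error is too small by the factor SD/√mean, and the actual size is 2 × [1 − Φ(1.96 / (SD/√mean))].

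| Outcome | Mean | SD | Variance/mean | Actual size |
|---|---|---|---|---|
| Glasgow | 70 | 15 | 225/70 = 3.21 | 27.4% |
| Glasgow | 75 | 15 | 225/75 = 3.00 | 25.8% |
| Glasgow | 80 | 15 | 225/80 = 2.81 | 24.3% |
| Rhinomanometry | 2.6 | 2 | 4/2.6 = 1.54 | 11.4% |
| Rhinomanometry | 1.6 (after an improvement of 1) | 2 | 4/1.6 = 2.50 | 21.5% |

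For example, at mean 70: 15/√70 = 1.793 and 1.96/1.793 = 1.093, so the size is 2 × [1 − Φ(1.093)] = 0.274.

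**3. Dependence on the SD.** At mean 75 the size is 9% for SD 10 and 40% for SD 20.

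**4. Simulation.** 100 per arm, means 70 and 80, SD 15, no interaction in points, 3,000 runs per setting. The table gives the rejection rate of the interaction test.

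| Covariate | Poisson, model-based | Poisson, robust | Linear |
|---|---|---|---|
| Binary 50/50, no effect of its own | 25.4% | 5.2% | 4.7% |
| Binary 30/70, no effect of its own | 26.4% | 5.6% | 4.9% |
| Continuous, no effect of its own | 26.2% | 5.5% | 4.8% |
| Binary 50/50, shifts the score by 10 points | 30.1% | 6.5% | 5.0% |

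The first three rows confirm step 2. In the last row the benefit in points is identical in both subgroups, so the excess under robust Poisson over linear regression reflects the change of scale.

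**5. The scale problem alone.** Assume control means of 60 and 75 in two subgroups and a benefit of 10 points in each. The ratios are 70/60 = 1.167 and 85/75 = 1.133, and the difference in logs is 0.154 − 0.125 = 0.029. With SD 15 and 50 per cell, its standard error is (15/√50) × √(1/60² + 1/70² + 1/75² + 1/85²) = 0.060. A correctly sized test would then reject in about 8% of trials, although there is no interaction in points.

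**6. Three modifiers.** At 25.8% per test, and if the tests were independent (an assumption), the chance of at least one false positive is 1 − (1 − 0.258)³ = 59%. This carries the same condition of model-based errors.

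**The case against.** The strongest reply is that the article names no variance estimator. A condensed article may leave robust or scaled errors to the full protocol or analysis plan. With them the false-positive rate is close to 5%, and the remaining scale effect is modest, about 6.5 to 8% in the settings tried. This stands, so the inflation can only be stated conditionally.

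A second reply is that the Poisson sentence speaks only of the effect of septoplasty. Secondary outcome measures also lists complications and side effects, which could be binary or counts. This stands in part. The paragraph that contains the sentence concerns quality of life and nasal passage, so the continuous reading is the natural one. If another outcome was meant, the text fails to name it.

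Three stronger readings are tempting, and the document supports none of them:

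- A reader might infer that every interaction test in this trial would have about 25% false positives. That rate belongs to a Glasgow score with mean 70 to 80 and SD 15 under model-based errors. Other outcomes and SDs give other rates, and no figures are given for peak flow.
- A reader might take it as fact that GBI scores can be negative and so rule the model out. The article says only that the GBI is sensitive to change. If negative values do occur, a standard Poisson fit would fail visibly; it would not quietly produce false modifiers.
- A reader might think that the main trial result is at risk. It is not: the primary effect is a mean difference and does not pass through this model.

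**Conclusion.** The point holds as a mismatch between the named model and the stated outcomes and effect scale. It is an explicit choice in the text, not a detail left open, and an analysis plan that followed the sentence would inherit it.

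Its size depends on the variance estimator. Under model-based errors, the plain reading, the nominal 5% test becomes about 24 to 27% on the protocol's Glasgow figures and about 11% for rhinomanometry at its stated mean and SD. Under robust errors the size is near 5%, but the test still concerns ratios of means while the trial reports differences. The possible failure with the GBI rests on the assumption that its scores can fall below zero.

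This should be fixed, but it is not critical: it concerns secondary analyses. It matters more than most secondary analyses because they are the stated reason for going from 48 and 70 to 100 per arm.

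**What to change.** Replace the Poisson sentence. For the continuous outcomes, specify linear regression with treatment, modifier and treatment-by-modifier terms. Adjust for the baseline score where a meaningful one exists, such as for the GHSI, rhinomanometry and peak flow. Do not adjust the GBI for a baseline score, because it measures change and is given after the intervention. Report each interaction as a difference in mean differences with its 95% confidence interval.

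If Poisson regression was intended for a binary or count outcome, name that outcome and specify robust variance.

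The cost is a sentence or two of protocol or analysis-plan wording. No patients, visits or data are affected. The article reports 110 of 200 participants enrolled at submission, so at that stage the change could be made well before the analysis.
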